## Abstract

**Introduction:**

Sexual violence is commonplace and has serious adverse consequences for physical and mental health. Sexual Assault Referral Centres (SARCs) are viewed as a best practice response. Little is known about their effectiveness and cost-effectiveness. Long-term data on the health and well-being of those who have experienced rape and sexual assault are also lacking.

**Methods and analysis:**

This is a mixed-methods protocol for a 1-year cohort study aiming to examine the health and well-being in survivors of sexual violence after attending a SARC in England. Quantitative measures are being taken at baseline, 6 and 12 months. Post-traumatic stress (PTS) is the primary outcome (target N=270 at 12-month follow-up). Secondary measures include anxiety, depression, substance use and sexual health and well-being. Using mixed-effects regression, our main analysis will examine whether variation in SARC service delivery and subsequent mental healthcare is associated with improvement in trauma symptoms after 12 months. An economic analysis will compare costs and outcomes associated with different organisational aspects of SARC service delivery and levels of satisfaction with care. A nested qualitative study will employ narrative analysis of transcribed interviews with 30 cohort participants and 20 survivors who have not experienced SARC services.

**Ethics and dissemination:**

The research is supported by an independent study steering committee, data monitoring and ethics committee and patient and public involvement (PPI) group. A central guiding principle of the research is that being involved should feel diametrically opposed to being a victim of sexual violence, and be experienced as empowering and supportive. Our PPI representatives are instrumental in this, and our wider stakeholders encourage us to consider the health and well-being of all involved. We will disseminate widely through peer-reviewed articles and non-academic channels to maximise the impact of findings on commissioning of services and support for survivors.

**Trial registration number:**

ISRCTN30846825.

Strengths and limitations of this studyThe study proposes the most substantial investigation to date in the UK of health, well-being and service utilisation in survivors of sexual assault and rape.The study applies a prospective, longitudinal design with a national sample of adults in England taking up Sexual Assault Referral Centres (SARC) services following experience of recent or non-recent sexual assault or rape, including all genders, to look at outcomes over 1 year.The study considers a wider definition of sexual health than just sexually transmitted infection acquisition.The study uses innovative approaches to recruitment that address barriers to research participation in the target population, including challenges created by COVID-19 and is supported by a wide range of stakeholders nationally including a group of people with lived experience of sexual violence and abuse.Relatively few survivors of sexual assault and rape have used SARCs, so generalisability to all people who have been exposed to sexual violence and abuse may be limited.

## Introduction

Sexual violence is commonplace, with evidence suggesting that one in five women and one in twenty-five men in England and Wales have experienced sexual assault since the age of 16.^1^ Sexual violence refers to any sexual act, or attempt at a sexual act, or an act directed at a person’s sexuality, involving coercion.^2^ Sexual violence includes but is not restricted to: rape, sexual assault, child sexual abuse, sexual harassment, rape within marriage and relationships, forced marriage, so-called honour-based violence, female genital mutilation, trafficking, sexual exploitation and ritual abuse.^2^ Sexual violence often goes unreported to the police, though recent shifts in the public understanding of sexual violence and developments that include the *#metoo* movement on social media have likely contributed to year-on-year increased rates of reporting.^3^ Prior to the COVID-19 pandemic, fewer than 1 in 6 victims of rape reported to the police. In the year ending June 2021, the number of sexual offences recorded by the police (164 763 offences) showed an 8% increase compared with the previous year.^4^

The serious and devastating effects of sexual violence are a well-documented public health burden.^5^ They include a range of immediate and long-term physical and mental health consequences. For women who have experienced sexual violence, physical health consequences include unwanted pregnancy, sexually transmitted infections (STIs),^5^ urinary tract infections, painful sex, chronic pelvic pain and vaginal bleeding.^6^ For male victims, physical health consequences include genital and rectal injuries and erectile dysfunction.^7^ The mental health sequelae of sexual violence have been found to be equally substantial across different population groups.^5 7–9^ Post-traumatic stress (PTS) is common among those who have experienced sexual violence,^10 11^ with incidence and severity being similar in men and women.^12^ Other mental health consequences include alcohol use disorders, eating disorders, anxiety, depression, self-harm and suicidality.^5^ In addition, experiencing mental health problems such as lifetime PTS is associated with increased risk of other long-term health conditions including hypertension, cardiovascular disease and gastrointestinal problems.^10^ Thus, sexual violence produces significant health burden, with the wider economic costs to society reaching over £12 billion per year.^13^

Given the substantial personal, societal and economic costs of sexual violence, an effective and consistent response for survivors is imperative. In the 2003 guidelines on the provision of care for victims of sexual violence, the WHO recommended that an initial response to survivors should include medico-legal and health services provided at the same time, in the same location and preferably by the same health practitioner. Policy-makers, commissioners and health workers have been encouraged to develop this model of service provision.^14^ In the USA for example, many states offer Sexual Assault Nurse Examiner programmes or Sexual Assault Response Teams to provide these recommended services. In England and other parts of the UK, there has been a steady growth in Sexual Assault Referral Centres (SARCs) as a best practice response for survivors after incidents of sexual assault or rape.^15^ SARCs, as a form of medico-legal and health service, are intended to coordinate all of the care and support needs for survivors. This may include crisis emotional support, forensic medical examination for the purposes of collecting evidence needed to prosecute alleged perpetrators, provision of emergency contraception and HIV Post-Exposure Prophylaxis, referral to sexual health and other healthcare services, referral for mental healthcare needs (eg, counselling and therapy) and to an independent sexual violence advisor (ISVA) for ongoing support, particularly if dealing with the criminal justice system. There are approximately 50 SARCs in England including a number of specialist paediatric sites,^16^ operating with considerable variation in their service models.^17^ Currently, little is known about the effectiveness and cost-effectiveness that the different service models may represent in addressing the physical and mental health outcomes for survivors of sexual violence outlined above. In addition, although the substantial negative impacts of sexual violence are well-documented^5^ much less is known about the longer-term health and well-being outcomes for survivors. One exception is a recent study in South Africa which followed up female rape survivors over 3 years and, controlling for confounding variables, has shown they had a 60% increased risk of contracting HIV in that time compared with control group women who had not been raped.^18–20^ Data related to models of care survivors receive and health outcomes remain limited, however. Similarly, there is a paucity of data on (mental) healthcare access after SARC^21^ and understanding of how different service user characteristics might moderate the benefits of attending SARC (and other specialist services for sexual assault and rape), in particular characteristics associated with social inequities and marginalisation (eg, considering service users of migrant and ethnic minority backgrounds, and sexual and gender minority communities). Furthermore, there is a lack of data on the experiences of male survivors^22^; those with a disability^21^ even though they are at greater risk of sexual violence^23^; interactions between sexual violence exposure and chronic mental health problems, and comorbidity of health outcomes; non-partner sexual violence^24^ and sexual health outcomes other than the acquisition of sexually transmitted infections (STIs).^25^

This mixed-methods cohort study is the first to consider the health outcomes and cost trajectories of those who attend SARCs in England. It aims to evaluate the relationship between SARC factors, subsequent care (follow on specialist sexual assault services and mental healthcare), and trajectories of PTS; the relationship between participant characteristics and trajectories of PTS; and finally, the role that participant characteristics may have in moderating the benefits of different SARC factors and subsequent care. It represents the first such study to consider the broader sexual health and well-being of survivors attending SARCs alongside other assessments of their health and mental well-being over time. We also report here how findings from our pilot study at one English SARC and our early data collection experiences have informed a revised research protocol.

## Methods and analysis

### Design and setting

This is a mixed-methods cohort study of mental, physical, sexual health and cost outcomes over 1 year in adult survivors of sexual assault and rape who have received care through SARCs in England. Quantitative measures are taken at baseline (no sooner than 4 weeks) and at 6 and 12 months post-baseline. A nested qualitative study is included (see the Qualitative study section). The study is part of the Multi-disciplinary Evaluation of SARCs for better Health (MESARCH) programme (1 September 2018 to 31 January 2023). The wider programme includes two Cochrane Reviews,^26 27^ and ‘mapping’ English SARCs, their structure and services, in addition to the study described here.

### Sampling, recruitment and procedures

We have recruited a stratified random sample of 15 of all the current practicing adult SARCs in England (approximtely 50 identified at the time of writing) with strata defined according to service delivery model, size and level of integration of services. To do this, we have drawn on national indicators of performance data collected by National Health Service (NHS) England and NHS Improvement,^15^ the commissioning body for SARCs, and data collected from SARCs as part of the wider MESARCH study.

Recruitment is taking place in three phases. First, service users aged 18 years and above presenting in person (or remotely since COVID-19) at any of the 15 participating SARCs are screened by SARC staff. People are excluded if, in exercising own judgement, the responsible member of SARC staff conducting screening anticipates a service user may encounter difficulties in providing informed consent due to severe mental health issues, cognitive impairment or learning disability. We also exclude those visiting from prison settings, as conducting follow-up assessments in prisons is outside the scope of the project. SARC staff complete a screen form for all those over 18 presenting to the service, recording basic demographic data, and offence and referral characteristics and indicating whether the person is eligible or not, with any reasons for exclusion noted. These screen forms are given an identification number, contain no identifying information, and are passed to the project team to provide an indication of the characteristics of the pool of service users pre-enrolment.

Because many SARCs refer on quickly to other voluntary sector agencies (ie, non-governmental organisations (NGOs)), for each participating SARC, we identified all linked support agencies and worked to engage them. The second phase of recruitment mainly takes place in that follow-on setting. When the person is referred to follow-on services, the identification number assigned at SARC travels with them. The study is introduced in that setting by trained staff from the agency, and if the person/service user expresses an interest in hearing more about the study, the staff member seeks consent to pass on contact details to the researchers. The identification number is also passed to the research team at this point, thus allowing the researchers to link the person/contact details with the SARC data obtained in the first phase.

In the final phase, the research team takes responsibility for contacting service users and inviting them to participate. Box 1 provides further detail on the recruitment procedure. SARC service users may also self-refer to the study or be referred to the study directly by SARCs. Anyone aged 18 years or over who has visited a SARC in England during the recruitment phase (2 years) since 1 August 2019 was eligible for enrolment via direct contact with the research team. Please note a separate study focused on those aged 13–17 years is also being conducted as part of the wider MESARCH programme.

Box 1Procedure for involving adult service users in the Multi-disciplinary Evaluation of Sexual Assault Referral Centres (SARCs) for better Health (MESARCH) cohort studyService user receives care from the SARC.SARC staff member screens service user for eligibility. All eligibility information is de-identified (assigned an identification number only) and conveyed to the project team using secure sharing platform.A referral is made by SARC to an independent sexual violence advisor (ISVA; usually based within a voluntary sector agency) for follow-on care in line with usual practice, and the research identification number is placed on the referral form. If the service user is not willing to be referred to other agencies, the SARC could provide more information about the study at this point.Within the voluntary sector agency, eligible service users are approached mainly by ISVAs, who provide brief explanation about the project and invite service users to consider being involved in the study. For those who express an interest in hearing more, consent is requested to pass contact details to the project team and the person’s research identification number is also included (‘Level 1’ consent completed).Additional approaches for enabling recruitment include (a) having members of the project team ready to speak by phone or video link to a service user if the SARC worker/ISVA believes this is an appropriate approach for a particular service user; (b) showing a short video message of invitation co-produced with our Lived Experiences Group which could be used by SARC staff/ISVA to explain about the project (available on our project website and accessible using a QR code on study brochure); (c) opening study up to self-referrals by survivors who have used SARCs in England during the study recruitment phase.Once the contact information has been passed on to the researchers, there is no more involvement of the SARC/ISVA except in circumstances such as the participant requires support and has agreed for us to notify the SARC/ISVA.A trained project team member makes contact within 1 week of receiving the research referral consent form from the SARC or ISVA, and contact is made in line with service user preferences for example by email, text or phone call.Once contact is made by the project team, the project team will follow recruitment and safety protocols, explain study purpose and gain full consent (‘Level 2’ consent).When consent to take part in the study is established (using email or text or signed consent form), baseline data are collected using a range of options. These include offering a structured telephone interview, a weblink to complete the data collection online, an interview in person or via video link. Those submitting baseline data will be considered ‘enrolled’ in MESARCH.Follow-up is undertaken according to the participants’ preferences at 6 and 12 months consistent with our previous work.^50^

### Number of participants required

At each of the 15 participating SARCs and via some self-referral, eligibility and basic sociodemographic data are collected on a total of 2500 individuals enabling us to compare our cohort sample with the wider population of service users at SARC. The primary outcome of interest for evaluating service user journeys after attending a SARC is PTS, measured using the PCL-5.^28^ Our interpretation of models based on the PCL-5 will focus on what constitutes a minimal clinically important difference (MCID) for PTS. Stefanovics and colleagues^29^ concluded that differences of approximately 0.5 of an SD could be deemed clinically important both cross-sectionally and for within-person change. Since our study involves neither randomisation nor placebo-control, our analyses will focus on change in PTS symptoms between baseline and follow-up. We will take recommendations of Stefanovics *et al*^29^ as quantifying the change-score group-difference we would expect which separates a treatment that is effective from one that is ineffective. Based on guidelines,^28^ we anticipate this MCID of 0.5 SD to approximate to a 10-point difference on the PCL-5 change-score; however, Stefanovics *et al*^29^ propose that an SD-based approach would be more robust and we also recognise that the magnitude of change in on the raw-scale metric will be influenced by the length of time between baseline and follow-up.

To allow for four levels in a predictor variable (eg, four types of SARC service provider); up to 10 covariates; two time points; an expected small-to-moderate Cohen’s f, which corresponds to the MCID for our primary outcome variable^29^; and an α error probability of 0.05, 270 participants would be required at study end to achieve a power (1−β error probability) of 0.90. Based on previous studies,^19 20^ our pilot work, and recruitment and retention to date, we estimate attrition at 20% by 12-month follow-up, requiring a baseline target of 338 individuals (see estimated flow of participants in figure 1). Participants who do not complete a 6-month follow-up will still be eligible to complete 12-month follow-up measures.

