### Data analysis

Our analysis will determine if variation in SARC service delivery and other healthcare specific to sexual violence is associated with different levels of improvement in trauma symptoms between baseline and the 12-month follow-up. Our favoured statistical approach will be to model ‘trajectories’ of PTS using mixed-effects regression (ie, multilevel modelling, using Stata’s suite of mixed-effects tools^37^). This framework will enable us to model variation in the improvement in PTS and make best use of the three waves of data available. In the eventuality that change appears non-linear, we will first explore the utility of incorporating varying times of follow-up and modelling time-since-baseline rather than data-collection-wave as the time axis, although we will be mindful of the potential for introducing bias by incorporating such a source of variation. We will also consider standard single-level regression models (eg, Ordinary Least Squares (OLS) regression, Analysis of Covariance (ANCOVA)) and model observed change in PTS between baseline and 12 months, instead using the 6-month wave to assist with the treatment of any missing data using multiple imputation. In addition, and where appropriate, we will accommodate the nested data structure of participants within SARC-centres using cluster-robust SEs. Similar analyses will be carried out for the secondary outcomes.

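### The 0.90 power is illustrated with SARC provider type, a SARC-level factor, but the calculation treats 270 participants as independent; with 15 SARCs the power is about 0.5 to 0.7

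*Protocol article*

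**What the plan says.** Under Number of participants required, the calculation is set up for "four levels in a predictor variable (eg, four types of SARC service provider", with "up to 10 covariates; two time points", a small-to-moderate Cohen's f tied to the 0.5 SD minimal clinically important difference (MCID), and "an α error probability of 0.05". The result is that "270 participants would be required at study end to achieve a power" of 0.90. The only inflation is for 20% attrition, which takes 270 to a baseline target of 338.

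Under Sampling, recruitment and procedures: "We have recruited a stratified random sample of 15 of all the current practicing adult SARCs in England". Under Data analysis, who runs the SARC (police, NHS, voluntary agency or private company) is listed among the SARC-level characteristics of stage 1. The same section says that, where appropriate, "we will accommodate the nested data structure of participants within SARC-centres using cluster-robust SEs".

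**The concern.** Provider type varies only between SARCs. The information about it comes mainly from the number of SARCs and from how alike outcomes are within a SARC, much less from the number of people. The Data analysis section recognises the nesting, but the sample-size paragraph has no term for it, although it uses a SARC-level factor as its example.

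The main analysis asks whether variation in SARC delivery and in follow-on care is associated with improvement in trauma symptoms. The findings are meant for commissioners, and the longer-term economic model is conditional on the cohort showing significant differences between delivery models. If a non-significant provider effect is read against 90% power, it will look like evidence that the models do not differ, and it could also stop that modelling.

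**Working it through.** **Inputs from the article:** 4 levels (numerator df 3), 10 covariates, alpha 0.05, power 0.90, N = 270 at 12 months, 15 SARCs, MCID 0.5 SD.

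**Not given, so assumed:** numeric f; ICC of PCL-5 change (0 to 0.05 used); equal SARC sizes, m = 270/15 = 18; provider types spread as evenly as possible (4/4/4/3).

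**1. The plan's own figure.** Attrition reproduces: 270/(1 − 0.20) = 337.5, or 338. The 270 cannot be reproduced from the stated inputs alone because f has no number, so I solved for it.
- ANCOVA with denominator df 270 − 4 − 10 = 256: power 0.90 needs noncentrality λ = 14.39, so f = √(14.39/270) = 0.231.
- Repeated-measures ANOVA, between factor, two time points, assumed f = 0.20 and correlation 0.5: λ = 270 × 0.04 × 2/(1 + 0.5) = 14.4, power 0.900.

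Both routes give λ of about 14.4 and neither has a cluster term. For comparison, a 0.5 SD range over four equal groups gives f = 0.177 (minimum), 0.186 (evenly spaced) or 0.25 (maximum), so 0.231 lies within what the MCID allows.

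**2. Allowing for SARCs.** Design effect DE = 1 + (m − 1) × ICC = 1 + 17 × ICC. Effective N = 270/DE, and λ becomes 14.39/DE. A factor that varies only between SARCs is tested on 3 and 15 − 4 = 11 df.

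| ICC | DE | Effective N | λ | Power, 3 and 11 df | Power, 3 and 256 df |
|---|---|---|---|---|---|
| 0 | 1.00 | 270 | 14.39 | 0.76 | 0.90 |
| 0.01 | 1.17 | 231 | 12.30 | 0.69 | 0.84 |
| 0.02 | 1.34 | 201 | 10.74 | 0.63 | 0.79 |
| 0.05 | 1.85 | 146 | 7.78 | 0.48 | 0.63 |

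The last column applies the design effect but keeps participant-level df, which flatters the design.

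**3. Sensitivity** (ICC 0.01 / 0.02 / 0.05 unless stated).
- Unequal SARC sizes, coefficient of variation 0.6, DE = 1 + (1.36 × 18 − 1) × ICC, 11 df: 0.66 / 0.58 / 0.42.
- f = 0.25, the largest the MCID allows, 11 df: 0.76 / 0.70 / 0.55, and 0.83 at ICC 0.
- f = 0.186, 11 df: 0.49 / 0.44 / 0.32.
- 14 denominator df (15 − 1), f = 0.231: 0.73 / 0.66 / 0.51.
- 25 SARCs evenly filled (m = 10.8, 21 df): 0.80 / 0.76 / 0.66.
- 50 SARCs evenly filled (m = 5.4, 46 df): 0.86 / 0.84 / 0.80.

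**4. Could more participants restore 0.90?** With 15 SARCs on 11 df, about 385 completers are needed at ICC 0, 515 at 0.01 and 775 at 0.02. At ICC 0.05 it cannot be reached: as N grows, λ tends to 15 × 0.0533/0.05 = 16.0, where power is about 0.81.

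**The case against.** The strongest reply is that the size of the shortfall is conditional. The article states no ICC, no numeric f, no denominator df and no final number of SARCs. At ICC 0 with participant-level df the 0.90 stands, and part of the loss at low ICC comes from using 11 df. That is fair for the exact values, which should be quoted as a range. It does not rescue the claim: with 15 SARCs, power on between-SARC df is below 0.90 even at ICC 0, and this holds on 14 df (0.80) and with f = 0.25 on 11 df (0.83).

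Self-referral is open to anyone who used a SARC in England, so the number of SARCs may exceed 15. This also stands, but the article describes such recruitment as limited and works mainly through the sampled centres. At f = 0.231, even 50 evenly filled SARCs stay under 0.90. Reaching it takes either participant-level df with an ICC at or near 0 (up to about 0.01 if f = 0.25), or f = 0.25 spread over all 50 SARCs with ICC up to about 0.02. Neither describes a test based on 15 SARCs.

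Provider type is only an example, and the stage 1 predictors also include uptake of follow-on care. True, and those participant-level predictors are much less affected. But provider type is the one example given, and it belongs to the main question.

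The article also says that interpretation will focus on the MCID. That helps, but it does not correct the power statement. Cluster-robust standard errors do not restore power either, and with about 15 clusters they need a small-sample correction.

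**Conclusion.** The concern holds. The stated 0.90 corresponds to 270 independent participants and does not apply to the predictor used to illustrate it. With 15 SARCs and f = 0.231, power for provider type is about 0.7 at ICC 0.01 and just under 0.5 at ICC 0.05. It is 0.76 if outcomes do not cluster at all. The mismatch can be seen from the article alone. Its exact size rests on the assumed ICC, the back-solved f, equal SARC sizes and a near-even split of provider types. Unequal sizes or an uneven split would lower power further; more SARCs through self-referral would raise it, at f = 0.231 to no more than about 0.86 at ICC 0.01.

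**What to change.** Keep N = 270 and rewrite the power statement:

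- Give the numeric f, and say that 0.90 applies to participant-level predictors with observations treated as independent.
- For SARC-level predictors, state power of about 0.5 to 0.7 for ICC 0.01 to 0.05 with 15 SARCs at f = 0.231, and show how it moves with f and with the number of SARCs actually represented.
- Estimate the ICC of PCL-5 change from the study's own data and report it beside the SARC-level results.
- Commit to reading SARC-level results as confidence intervals against the 0.5 SD margin, so that non-significance is not reported as absence of a difference between delivery models.

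The cost is a reworded paragraph and a less favourable stated power. No participants are added and the planned models do not change.
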